#### Oral Glucose Tolerance Test

A standard 75 g oral glucose tolerance test will be performed with blood sampling at 0, 30, 60, 90, and 120 minutes. The test will assess dynamic changes in substrate metabolism, including ΔRQ shifts over time (120–60–0 min) and changes in circulating free fatty acids (ΔFFA), glucose, and insulin levels in response to the glucose load.

#### Hyperinsulinemic-Euglycemic Clamp

A 2-step hyperinsulinemic-euglycemic clamp will be conducted over 200 minutes, with insulin infusion rates of 10 and 40 mIU/m², each maintained for 100 minutes. This will be followed by a 100-minute tapering period of glucose infusion after insulin discontinuation. The primary outcomes will include ΔRQ (at 300–250–200–100–0 min), free fatty acid suppression (ΔFFA), and glucose infusion rate (ΔGIR) as markers of insulin sensitivity and MetFlex.

#### Maximal Oxygen Uptake Test

A graded maximal exercise test will be performed on a bicycle ergometer (Ergoline GmbH) using a ramp protocol with an incremental workload increase of 15 W/min. Gas exchange parameters will be measured continuously via spiroergometry (Quark RMR), and electrocardiogram monitoring will be conducted throughout the test. The primary outcomes (maximal oxygen uptake [VO₂max], heart rate, and peak power output), will be used to individualize the exercise intervention protocol.

#### Diet Record

Each participant will provide a 3-day diet record before the intervention or control period, once during the period, and then after the completion of the intervention or control. Nutrixo (Arcai Health) software with validated food composition databases will be used to calculate dietary intakes.

#### Metagenomics Analysis of Gut Microbiota

The microorganism populations present in the stool samples will be assessed by shallow shotgun sequencing using NovaSeq ox NextSeq Illumina platform targeting sequencing depth of approximately 1 million reads or samples. Demultiplexing, BAM and FASTQ file generation will be performed using the Picard suite (Broad Institute). Quality-filtered metagenomes will be taxonomically profiled using MetaPhlAn3 (Metagenomic Phylogenetic Analysis) with default parameters.

#### Untargeted Analysis of Serum Metabolome

Serum metabolite spectrum will be determined using NMR-based methods. Serum samples will be analyzed on Bruker AVANCE III 600 MHz and 700 MHz spectrometers according to the standard protocols. Metabolites will be identified by comparison with spectral databases (BBIOREFCODE, Chenomx, HMDB [Human Metabolome Database]) and published assignments. Liquid chromatography–mass spectrometry analysis in serum extracts will be performed using previously optimized procedures including extraction, separation by liquid chromatography (Agilent 1200), and detection by Bruker MS spectrometer micrOTOF-Q III. Suitable conditions will allow identification per exact mass, retention time, isotopic pattern, and fragmentations. For this purpose, Bruker software and MZmine 2.17 will be used.

### Data Analysis and Statistical Considerations

To assess the effectiveness of the weight loss intervention and identify key predictors of response, such as microbiome, metabolomic profiles, and demographics, we will use generalized mixed effects models. These models account for both fixed effects (the intervention and relevant covariates) and individual variability, providing a robust analysis of the impact of the intervention. In addition, we will develop elastic net-based predictive models, complemented by machine learning algorithms, to stratify individuals into intervention groups, with the secondary aim of identifying responders. These models will be subjected to rigorous validation, including cross-validation or bootstrapping, to ensure their accuracy and generalizability. This approach aims not only to determine the efficacy of the intervention but also to improve personalized treatment by accurately classifying individuals based on their unique profiles, thereby advancing the field of personalized medicine. The analyses will be performed using IBM SPSS Statistics and R statistical packages.

### Sample Size

Sample size considerations will be based on the power to address the primary hypothesis. The main predictor variables for the sample are ΔRQ (200-0) and glucose disposal (mg/kg/min). In recent observations from our TRIEMA (Treatment of Insulin Resistance: a Personalized Approach) study (NCT03710850), glucose disposal was 6.6 (SD 2.1), while ΔRQ was 0.05 (SD 0.04). The dependent variable, the expected weight loss after the intervention, is 4 (SD 5) kg [20]. The 30-subject study will have 80% power to detect a difference in weight loss of 4 kg (which is a clinically significant 5% weight loss for a woman weighing 80 kg at a difference of ΔRQ=0.07 (calculated using the PWRSS library in the R environment), at a probability level of *α*=.05. We plan to enroll 40 women to allow for attrition to the end of the intervention without risk of losing statistical power.

### Major Confounders

It is known from the literature that people who start a structured exercise program may experience behavioral compensation in the form of increased food intake [21] and reduced habitual physical activity in everyday life [22,23]. Therefore, in our study, we will monitor participants’ caloric intake using repeated 24-hour recalls and physical activity using an accelerometer. Caloric intake and habitual physical activity will always be assessed (1) in the week before the exercise intervention, (2) in the 6th week of the intervention, that is, after reaching the target energy expenditure, and (3) in the last 12th week of the intervention. In each of these weeks, caloric intake is assessed using 24-hour menu records from 3 specific days (the day of exercise, a weekday without exercise, and the weekend), using an application that works with validated food composition tables [24]. The caloric intake for each of the 3 weeks will be calculated from these 3 days.

Physical activity will be assessed in each of the specified weeks using the Axivity AX3 accelerometer. The accelerometer will be attached to the participant’s wrist and worn within 24 hours for 7 full days. The data from the accelerometer will be processed using the GGIR library in R and the volume (average acceleration) and intensity (intensity gradient) of physical activity [25] will be calculated for each of the 3 weeks.

Compensation will be calculated as the difference between caloric intake or physical activity during the intervention (average of weeks 6 and 12) and before the intervention.

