### Intervention

The exercise intervention is designed according to the 2021 European Association for the Study of Obesity (EASO) guidelines to maximize the effect of reducing body weight and adipose tissue [17]. These guidelines recommend 150 to 200 minutes of at least moderate-intensity aerobic exercise (Grade A). The exercise intervention will last 12 weeks, during which the study participants will perform aerobic endurance exercise 3 times a week in groups of 6 people under supervision.

The exercise will be performed as fast walking on a treadmill. The duration and intensity of the exercise will be controlled so that the energy expenditure per unit of exercise is 150 kcal in the first week, increasing by 50 kcal each week thereafter until week 6 when it reaches 400 kcal, a level that will be maintained until the end of the intervention [18]. The walking pace will be adjusted individually, based on input of indirect calorimetry, to correspond to moderate intensity physical activity (metabolic equivalent of task 3 to 6) and to achieve the required energy expenditure in the given time. A progressive increase in energy expenditure during the intervention will be therefore ensured by an appropriate combination of increasing intensity and duration of exercise. For this reason, the duration of each session will be individual, for example, 30 minutes of walking at a speed of 5 km/hour corresponds to approximately 180 kcal for a person weighing 95 kg [19].

During the intervention, participants’ compliance will be strictly monitored: if a session is missed, it will be made up as soon as possible. If more than one session is missed (eg, due to illness), the intervention will be extended to make up for the missed sessions, but not more than 2 weeks. Only participants who complete at least 90% of the training sessions will be included in the analysis (so they can skip a maximum of 3 sessions).

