## Discussion

This randomized trial will assess the strength of predictive factors associated with successful weight loss after an exercise intervention in women with obesity. By focusing on both whole-body and gut MetFlex, the study aims to elucidate key mechanisms that contribute to individual variability in weight loss outcomes. The findings have the potential to lead to the development of more personalized and effective weight loss treatments, filling a critical gap in current obesity and diabetes management.

Several key decisions were made in the design of this clinical trial to overcome limitations in existing literature and reduce potential bias. One such decision is the use of a cross-over trial design, which enhances the robustness of the study by allowing participants to serve as their own controls. This approach helps reduce interindividual variability and provides stronger evidence of the causal relationship between the interventions and the observed outcomes.

Lifestyle interventions, particularly those combining dietary and exercise components, are as essential for managing and potentially reversing diabetes progression [27,28]. Substantial evidence supports the role of sustained weight loss in improving insulin sensitivity, glycemic control, and other metabolic outcomes. However, the heterogeneity in response to such interventions highlights a critical need for personalization [29,30]. Individuals vary widely in their ability to lose weight and maintain that loss, which is often attributed to differences in MetFlex, the gut microbiome, and behavioral adaptations [31]. An additional strength of this study is the comprehensive monitoring of participants’ dietary intake and physical activity throughout the intervention. By accounting for compensatory behaviors, such as changes in caloric intake or reduced physical activity outside of exercise sessions, we aim to provide a clearer understanding of how these factors contribute to weight loss variability.

However, some limitations need to be considered. The strict eligibility criteria may make recruitment challenging, potentially limiting generalizability to the broader population of women with obesity. Furthermore, while compensatory behaviors are monitored, other factors such as psychological and social influences could still impact outcomes.

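### Activity compensation is computed from full-week accelerometer values that include the supervised sessions, so it understates, and can mask, the fall in habitual activity it is meant to measure

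*Protocol article*

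**What the plan says.** The Major Confounders section of the protocol article gives the reason for measuring activity: women who start structured exercise may show "reduced habitual physical activity in everyday life". The Discussion presents this monitoring as a strength and describes the target as "changes in caloric intake or reduced physical activity outside of exercise sessions".

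Major Confounders then fixes the measurement. The wrist accelerometer is "worn within 24 hours for 7 full days" in each of three weeks: the one before training starts, week 6 and week 12. From these data "the volume (average acceleration) and intensity (intensity gradient) of physical activity [25] will be calculated for each of the 3 weeks". The score is defined in one sentence: "Compensation will be calculated as the difference between caloric intake or physical activity during the intervention (average of weeks 6 and 12", minus the value before the intervention.

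The Intervention section says that participants will "perform aerobic endurance exercise 3 times a week in groups of 6 people under supervision". Energy expenditure per session rises to 400 kcal by week 6 and stays there to the end. Neither section says that the device comes off during training or that session time is removed from the record.

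**The concern.** The quantity wanted is the change in everyday activity outside training. The quantity defined is the change in all activity over the week, and only the two intervention weeks contain training. A woman whose daily life does not change at all gets a positive score. A woman who cuts back gets a score that is too high, and it can sit at zero or above if her cut is small enough.

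At stake is the explanatory use the Discussion announces, which is to show how compensatory behaviour contributes to differences in weight loss. If the activity score is partly a measure of the training itself, statements about how many women compensated, and by how much, will be too favourable.

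**Working it through.** The article gives no numerical figure for compensation, so the check is a reading of the formula plus arithmetic.

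**Inputs from the article (Intervention)**
- Session dose: 150 kcal in week 1, plus 50 kcal a week. Week 6 is 150 + 5 × 50 = 400 kcal, which agrees with the stated 400 kcal.
- Three sessions a week.
- Worked example: 180 kcal in 30 minutes at 95 kg, so 180/30 = 6 kcal/min.
- Permitted intensity: 3 to 6 MET.

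**Session time in weeks 6 and 12**
- Minutes per session: 400/6 = 66.7.
- Minutes per week: 3 × 66.7 = 200.
- Share of the recorded week: s = 200/10,080 = 0.0198, or 2.0%.
- Prescribed expenditure: 3 × 400 = 1,200 kcal a week, absent from the reference week.
- Taking 1 MET as 1 kcal/kg/h at 95 kg, 3 MET gives 400/(3 × 95/60) = 84.2 min per session, 253 min a week (2.5%). 6 MET gives 42.1 min per session, 126 min a week (1.3%).

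**What the score measures**

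Let B be mean acceleration in the reference week, H mean acceleration outside sessions during the intervention, and W mean acceleration within sessions. Then

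score = H(1 − s) + W·s − B.

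With no compensation (H = B) this is s(W − B). It is positive whenever a session is more active than the average minute of the week, which includes sleep. The correct value would be zero.

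**Size of the shift**

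W and B are not in the article and are assumed here: W = 100-200 mg, B = 25-30 mg.
- Low end: 0.0198 × (100 − 30) = 1.4 mg; 1.4/30 = about 5%.
- High end: 0.0198 × (200 − 25) = 3.5 mg; 3.5/25 = about 14%.

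These figures are net of the habitual activity that the session minutes displace.

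**Effect on a true fall in habitual activity (assumed B = 25 mg)**

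| True fall | Score, W = 60 mg | Score, W = 100 mg | Score, W = 150 mg | Sessions removed |
|---|---|---|---|---|
| 0% | +2.8% | +6.0% | +9.9% | 0% |
| 5% | −2.1% | +1.1% | +5.0% | −5% |
| 10% | −7.0% | −3.8% | +0.1% | −10% |
| 20% | −16.8% | −13.7% | −9.7% | −20% |

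Small falls are masked or change sign; larger ones are understated. With the session windows removed, the true value is recovered in every row.

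The intensity gradient is likely to move as well, because moderate-intensity minutes are added. The article gives nothing from which to size that.

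**The case against.** **The article may simply be silent on a processing step.** Cutting out session windows is a detail that a full protocol or analysis plan could hold, and the section does speak of habitual activity. This carries some weight. But the article is not silent on the calculation: it fixes the wear time, the metrics, the weeks and the subtraction. Followed as written, those rules give the shifted score. If a fuller document already removes the sessions, the article's sentence still needs to say so.

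**A constant shift would leave associations intact.** If every woman's score rose by the same amount, only the mean and the zero point would move, and the relation between compensation and weight loss would be unchanged. The fixed 400 kcal dose and the 90% attendance rule push that way, and faster walking shortens the session. This stands in part. Pace and duration are set individually, so the shift may differ between women, but the article does not allow that difference to be sized. A reader might infer that the explanation of weight-loss variability would come out reversed. That is not shown.

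**Energy is not acceleration.** A reader might also infer that a woman who cuts 1,200 kcal a week from daily life would score zero. That requires a kilocalorie lost in daily life and one spent on a treadmill to produce equal wrist acceleration, and nothing in the article supports it.

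**No model is said to use the score as a covariate.** The section heading calls these variables confounders although they arise after training starts, and the Discussion says "By accounting for compensatory behaviors, such as changes in caloric intake or reduced physical activity outside of exercise sessions". A reader might infer that the Stage 1 slope will be adjusted for compensation and so biased. The data analysis section refers only to relevant covariates and does not name compensation, and the use described in the Discussion is explanatory. The objection stands: the documents do not support a claim of bias in the Stage 1 or Stage 2 model.

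**Conclusion.** The point holds as a defect in a stated calculation. The activity score mixes prescribed training with habitual activity, contrary to the target in the Discussion. The direction is upward for average acceleration, provided only that sessions are more active than the average recorded minute.

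From the article's own figures, the contaminating time is about 200 minutes a week, 2.0% of the record (1.3% to 2.5% across the permitted intensity range at 95 kg). The size in acceleration units, about 1.4-3.5 mg or 5-14%, rests entirely on the assumed 100-200 mg in sessions and 25-30 mg otherwise. At a lower session acceleration of 60 mg with a 30 mg baseline it would be 0.0198 × 30 = 0.6 mg, or 2%.

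It would be too strong to say that compensation is always hidden. Masking is complete only when the habitual fall is no larger than the session contribution. The consequence is limited: the intake half of the formula is untouched, and compensation is not among the listed primary, secondary or exploratory outcomes. It is worth correcting because the article claims this monitoring as a strength.

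**What to change.** In Major Confounders, define activity compensation on session-free data:
- Log the start and stop time of every supervised session in weeks 6 and 12.
- Remove those windows in GGIR, and the matching clock times in the pre-intervention week, before computing average acceleration and intensity gradient.
- Take the mean of weeks 6 and 12 minus the pre-intervention week on the cleaned values.
- Report total activity, sessions included, as a separate quantity.

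The cost is a session log and a small change to the processing script; no new measurements are needed. Logging should start now: recruitment is ongoing and 12 women are randomized, six of whom have already finished the A-arm intervention. Their raw recordings can be reprocessed this way only if session times were kept or can be reconstructed. Otherwise, non-training days compared with the same weekdays at baseline offer a fallback.

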### Feasibility Consideration

The team has extensive experience in conducting clinical trials and all methods are routinely available in the team members’ facilities. Therefore, we do not anticipate any feasibility issues. We anticipate difficulties in recruitment and enrollment due to the challenging protocol and strict inclusion and exclusion criteria and anticipate a buffer time in the timetable for up to double the recruitment of participants. In case of an emergency situation that would make it impossible to carry out the clinical trial (such as the experience during the COVID-19 pandemic), we plan to work within work package 2 with databases and biobank material from previous studies that would allow the project outputs.

### Ethical Considerations

The institutional review board of the University Hospital (EK-VP/28/1/2022) and the Faculty of Physical Education and Sport of Charles University (218/2023) reviewed the protocol before recruitment, and all participants will sign an informed consent form before enrollment. The study will be conducted in accordance with the Declaration of Helsinki and GCP.

The study will be conducted in accordance with the Declaration of Helsinki and Good Clinical Practice (GCP). The protocol was reviewed by the institutional ethics committee of University Hospital Kralovske Vinohrady and the Faculty of Physical Education and Sport Charles University.

## Results

Recruitment for the trial began in January 2024. A total of 12 participants were enrolled and randomized. Among them, 6 participants have completed the first phase of the A-arm and 6 participants have completed the control period of the B-arm and their intervention is ongoing. Recruitment is ongoing. We expect the preliminary data from this study to be completed in 2026. This clinical trial protocol was developed based on the SPIRIT (Standard Protocol Items: Recommendations for Interventional Trials) 2013 Statement [26] (Multimedia Appendix 1).

## Discussion

This randomized trial will assess the strength of predictive factors associated with successful weight loss after an exercise intervention in women with obesity. By focusing on both whole-body and gut MetFlex, the study aims to elucidate key mechanisms that contribute to individual variability in weight loss outcomes. The findings have the potential to lead to the development of more personalized and effective weight loss treatments, filling a critical gap in current obesity and diabetes management.

Several key decisions were made in the design of this clinical trial to overcome limitations in existing literature and reduce potential bias. One such decision is the use of a cross-over trial design, which enhances the robustness of the study by allowing participants to serve as their own controls. This approach helps reduce interindividual variability and provides stronger evidence of the causal relationship between the interventions and the observed outcomes.

Lifestyle interventions, particularly those combining dietary and exercise components, are as essential for managing and potentially reversing diabetes progression [27,28]. Substantial evidence supports the role of sustained weight loss in improving insulin sensitivity, glycemic control, and other metabolic outcomes. However, the heterogeneity in response to such interventions highlights a critical need for personalization [29,30]. Individuals vary widely in their ability to lose weight and maintain that loss, which is often attributed to differences in MetFlex, the gut microbiome, and behavioral adaptations [31]. An additional strength of this study is the comprehensive monitoring of participants’ dietary intake and physical activity throughout the intervention. By accounting for compensatory behaviors, such as changes in caloric intake or reduced physical activity outside of exercise sessions, we aim to provide a clearer understanding of how these factors contribute to weight loss variability.

However, some limitations need to be considered. The strict eligibility criteria may make recruitment challenging, potentially limiting generalizability to the broader population of women with obesity. Furthermore, while compensatory behaviors are monitored, other factors such as psychological and social influences could still impact outcomes.

In conclusion, this trial will provide important insights into the role of MetFlex and the gut microbiome in predicting successful weight loss. These findings could lead to more personalized interventions in clinical practice, ultimately improving adherence and outcomes in obesity and diabetes management.

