## Methods

### Design

A randomized, cross-over, controlled clinical trial will be conducted at Charles University in Prague, Czech Republic. The study will consist of a two-stage analytical approach that will be used to obtain specific results:

1. The first stage is a predictive validation study where we will compare changes in fat mass (FM)/ fat-free mass (FFM) weight loss (after an intervention - predictor variable) with baseline characteristics (independent variable) in the whole sample (n=40). The expected results are the identification of baseline characteristics associated with total and FM/FFM weight loss after the intervention.

2. The second phase is a 2:1 randomized cross-over control trial where we will investigate the effects of the progressive aerobic exercise intervention protocol on MetFlex, metabolic adaptation, and insulin sensitivity. As an exploratory outcome, the fecal metabolomic response will be analyzed.

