### Allocation

After screening for eligibility, a baseline clinical examination will be performed to assess the inclusion and exclusion criteria and to ensure weight stability for 12 weeks before enrollment. Participants will then be randomized by an independent investigator to either exercise intervention arm A or exercise intervention and control arm B using a computer-generated random number table.

After the baseline visit 1 examination, the A-arm will undergo 12 weeks of a progressive aerobic exercise intervention protocol, after which the clinical examination will be repeated. Participants in the B-arm will be assessed after 12 weeks of no intervention and then crossed over to the exercise intervention, after which the final clinical assessment will be carried out (Figure 1).

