### Primary Outcome Measures

Stage 1: the relationship between FM/FFM weight loss and baseline characteristics of MetFlex, calculated as the change in respiratory quotient (ΔRQ).

Stage 2: change in MetFlex, defined as the ΔRQ between basal and insulin-stimulated state during glucose clamp examination, and change in insulin sensitivity (glucose infusion rate).

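### Stage 2 is labelled a cross-over, but the design described is a one-way delayed start: own-control data exist only in arm B and are confounded with time

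*Protocol article*

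**What the plan says.** The Design section states: "The second phase is a 2:1 randomized cross-over control trial". The Abstract uses the same label.

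The Allocation section gives the sequences. Women are "randomized by an independent investigator to either exercise intervention arm A or exercise intervention and control arm B". For arm A, "the A-arm will undergo 12 weeks of a progressive aerobic exercise intervention protocol, after which the clinical examination will be repeated". For arm B, "Participants in the B-arm will be assessed after 12 weeks of no intervention and then crossed over to the exercise intervention".

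The Discussion draws a benefit from the label. The design "enhances the robustness of the study by allowing participants to serve as their own controls", and: "This approach helps reduce interindividual variability and provides stronger evidence of the causal relationship between the interventions and the observed outcomes".

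The outcome at issue is primary. Primary Outcome Measures lists "Stage 2: change in MetFlex, defined as the ΔRQ between basal and insulin-stimulated state during glucose clamp examination", together with change in insulin sensitivity. On the model, Data Analysis and Statistical Considerations says: "These models account for both fixed effects (the intervention and relevant covariates) and individual variability".

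**The concern.** In a two-sequence cross-over, half the sequences run treatment then control and the others control then treatment. Time effects can then be separated from treatment, and each woman's own contrast contributes. Here the only sequence with both conditions is control then exercise. What is randomised is when exercise starts, not the order of two conditions.

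Two consequences follow. First, the own-control property claimed in the Discussion cannot apply to arm A as the Allocation section describes it. The 12 weeks of weight stability before enrolment are an eligibility check, not a control period with clamp measurements. Second, in arm B any change over calendar or study time, such as familiarity with repeated clamps, is carried into the comparison of exercise with control.

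The stake is the Stage 2 effect on metabolic flexibility and insulin sensitivity. An analyst who takes the Discussion at its word would lean on within-woman change, which the randomisation does not protect, instead of the between-arm comparison, which it does.

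**Working it through.** **1. The plan's own figure.** Sample Size gives N = 30 for 80% power, from a 4 kg weight difference at a ΔRQ difference of 0.07, SD of ΔRQ 0.04, SD of weight loss 5 kg, α = 0.05 (two-sided assumed).
- Slope = 4/0.07 = 57.14 kg per unit ΔRQ; r = 57.14 × 0.04/5 = 0.457; R² = 0.209; f² = 0.209/0.791 = 0.264.
- N = (1.960 + 0.842)²/0.264 = 29.7, i.e. 30 (normal approximation; an exact F test gives 32).

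The figure is a Stage 1 regression and uses no cross-over gain. No separate Stage 2 sample size is given.

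**2. What the cells identify.** Write τ for the exercise effect and π for the time difference between the two periods.

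| | Weeks 0–12 | Second 12 weeks |
|---|---|---|
| Arm A | exercise | none described |
| Arm B | control | exercise |

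- A minus B, first period: τ (randomised).
- B second period minus B first period: τ + π.

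If arm B's change under exercise is compared with its change under control, a constant drift cancels and only unequal drift biases the result. In both forms, lack of bias is an assumption about time, not a result of randomisation.

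**3. Information on τ.** I used a random-intercept model with cells A: baseline, exercise and B: baseline, control, exercise, in units of total variance. The split of 20:10 completers and the within-woman correlation ρ are assumptions.

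With visit effects, the last visit has its own mean and only exercising arm B women are seen there, so it carries nothing about τ. The variance is (1/20 + 1/10)(1 − ρ²) with or without that visit. A true two-sequence cross-over of the same size, ignoring carry-over, has variance (1/20 + 1/10)(1 − ρ)/2.

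| ρ | With B's exercise period | Without it | True cross-over | Ratio |
|---|---|---|---|---|
| 0.3 | 0.1365 | 0.1365 | 0.0525 | 2.6 |
| 0.5 | 0.1125 | 0.1125 | 0.0375 | 3.0 |
| 0.7 | 0.0765 | 0.0765 | 0.0225 | 3.4 |
| 0.9 | 0.0285 | 0.0285 | 0.0075 | 3.8 |

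The with and without columns also agree at 27:13 and at 10:20. Only if time effects are set to zero does B's second period help (0.0298 against 0.0450 at 20:10, ρ = 0.5).

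**4. Precision of the randomised contrast.** For a two-sample t test, 20 versus 10, two-sided 5%, the noncentral t gives 80% power at 1.124 SD. With SD 0.04 this is 1.124 × 0.04 = 0.045 in ΔRQ. With baseline adjustment at ρ = 0.5 it is 0.045 × √(1 − 0.25) = 0.039. The mean ΔRQ quoted in Sample Size is 0.05.

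**5. Hypothetical illustration of bias.** Suppose exercise pre-post changes were pooled in 30 women with no period term and exercise had no effect. Take SD of change 0.04 (equal to SD 0.04 with ρ = 0.5) and an assumed time shift of 0.01 to 0.02 in ΔRQ. The paired t test has noncentrality (0.01/0.04)√30 = 1.37 to (0.02/0.04)√30 = 2.74, so it rejects 26% to 75% of the time. The document gives no shift and does not plan this test.

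**The case against.** Several stronger readings are tempting and are not supported.

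- *The own-control benefit is wholly absent.* Arm B women are observed under both conditions, and their contrast does remove between-woman variance. What it lacks is protection against time effects. Baseline values in both arms can also be used for adjustment.
- *The planned model will count time trends as exercise effect.* The analysis section names the intervention and relevant covariates; it neither includes nor excludes a visit term. This is a condensed article, and such detail may sit in an analysis plan that is not shown. Silence on a period term is not itself an error, so the rejection rates in step 5 of the working illustrate a risk and do not describe the plan.
- *Two thirds of the women have no control period.* The article does not say which arm takes the larger share, and Results mentions 6 women in each arm. If 2:1 means B:A, about 27 of 40 women have own-control data. The order is still fixed and still confounded with time.
- *Arm A women leave after 12 weeks.* This is not stated. Results speaks of a first phase of arm A, and Figure 1 is not shown. No later arm A phase is described, however.
- *Stage 2 cannot give a valid effect, or the sample size fails with it.* The first 12 weeks are an intact randomised comparison, and the N of 30 belongs to Stage 1.

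It is also fair to say that marked regression to the mean in ΔRQ is not expected, since eligibility does not select on it, and that rolling recruitment means study period is not one calendar season. These points lower the likely size of a time effect. They do not make arm B's comparison randomised.

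**Conclusion.** The point holds as a conflict within the article. The cross-over label, and the own-control and causal-evidence claims in the Discussion, do not fit the sequences in the Allocation section. Own-control data are confined to arm B: about 13 of 40 enrolled or 10 of 30 completers if 2:1 means A:B. They are unbiased only if time effects are absent, or equal in both periods for change-minus-change.

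With visit effects modelled, the exercise effect rests entirely on A versus B over the first 12 weeks. Its variance is about 2.6 to 3.8 times that of a true cross-over of the same size over correlations of 0.3 to 0.9. That zero information comes from arm B's exercise period does not depend on the split or correlation. The detectable differences do: they assume 20:10 completers, SD 0.04 and, for 0.039, a correlation of 0.5.

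**What to change.** - Relabel Stage 2 as a randomised delayed-start (wait-list) trial wherever it is called a cross-over, and state which arm takes the larger share of the 2:1 allocation.
- Make the primary Stage 2 estimate A versus B at week 12, by ANCOVA on the week-12 value adjusted for the visit-1 value.
- If all visits enter one mixed model, include a visit or period effect.
- Present arm B's control-to-exercise comparison as supportive, with its assumption about time stated.
- In the Discussion, remove or limit the sentences on own controls and stronger causal evidence.

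The cost is wording in the protocol and analysis plan, with no new data. Recruitment was still open with 12 women randomised when the article was written. The downside is that the precision that can be claimed for Stage 2 becomes less favourable.
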